# Impact of a smartphone application (KAIA COPD app) in combination with *A*ctivity *M*onitoring as a maintenance pr*O*gram following *PU*lmonary *R*ehabilitation in COPD: the protocol for the AMOPUR Study, an international, multicenter, parallel group, randomized, controlled study

**DOI:** 10.1186/s13063-020-04538-1

**Published:** 2020-07-11

**Keywords:** Physical activity, Smartphone application, KAIA COPD, COPD, Digital therapeutics, Maintenance, Medical mobile application

## Abstract

**Background:**

Increasing physical activity (PA) is considered to be an important factor for the efficient management of chronic obstructive pulmonary disease (COPD). Successful methods required to achieve improvements in PA following pulmonary rehabilitation (PR), however, are rarely reported. Therefore, we will conduct this trial to evaluate the effectiveness of using a COPD management program delivered to the patient via the KAIA COPD app, a mobile medical application, after the completion of PR.

**Methods:**

This is the protocol for a randomized, controlled, open-label, multicentered trial that will be carried out at inpatient PR hospital centers in Germany and Switzerland. The interventions will involve the use of the KAIA COPD app program (Arm 1) or an active comparator, i.e., usual care (Arm 2). Patients completing an in-hospital PR program and consenting to participate in the study will be screened with the inclusion and exclusion criteria and enrolled in the study. After fulfilling the screening requirements, the patients will be randomized into one of the two arms with parallel group assignment in a 1:1 ratio. The training program will be delivered to the participants grouped in Arm 1 via the KAIA COPD app and to participants grouped in Arm 2 via the regular recommendations or standard of care by the PI. In total, 104 participants will be included in the trial. The treatment period will last for 24 weeks. Electronic versions of questionnaires will be used to collect patient-reported assessments remotely. The primary outcome measure is the change in physical activity of the intervention group in comparison to the control group, measured over 1 week as the mean steps per day with a Polar A 370 activity tracker, from baseline (end of PR) to the 6-month follow-up. The secondary outcome measures are functional exercise capacity, health status, sleep quality, exacerbation rate, and depression and anxiety symptoms assessed at several intervals.

**Discussion:**

This study seeks to prove the effects of the KAIA COPD mobile application in COPD patients after PR. The app offers educational, exercise training plus activity monitoring and motivational programs that can be easily implemented in the patient’s home setting, enabling patients to maintain the effects that are typically elicited in the short term after pulmonary rehabilitation for the long term.

**Trial registration:**

German Clinical Trials Register (DRKS00017275). Protocol version 2.0 dated 3 June 2019.

## Introduction

### Background and rationale {6a}

Exercise training is an important component in the management of COPD. Numerous trials have shown large improvements in health-related quality of life (HRQoL) and exercise capacity in subjects with COPD following structured exercise training within a pulmonary rehabilitation (PR) program [1]. However, despite the well-known benefits of exercise training, the great majority of patients who would benefit from PR are often not referred to such a program. The proportion of COPD patients who are not transferred to available pulmonary rehabilitation programs or who do not complete them is estimated to vary between 8 and 50% and between 10 and 32%, respectively [2]. Major barriers for not participating in or adhering to PR include travel and transport, disruption to an established routine, lack of perceived benefits, being socially isolated, and lack of social support, inconvenient timing, influence of health care provider, illness and comorbidities, current smoking, and depressive symptoms [3–5]. Additionally, for patients who undergo a supervised exercise training program, it is often challenging to implement a follow-up program or regular exercise training into their daily life home settings. Consequently, many COPD patients are either not instructed to exercise at all or fail to adhere to exercise training at home after completing PR [6].

Traditionally, PR programs are provided under direct supervision at a rehabilitation center with participants attending PR in an inpatient or outpatient setting. However, both community-based and home-based programs are becoming increasingly popular [6]. Of the studies included in the most recent systematic review of pulmonary rehabilitation in COPD patients [1], approximately 25% were home-based programs (*n* = 15) or included an element of home-based training along with an inpatient or outpatient program (*n* = 9). Many of the studies relied on supervision by medical staff in regular visits to a hospital or clinic for additional exercise training sessions, home-based visits, or telephone calls [7–13]. However, the strong effects detected immediately after completion of the exercise training programs either decreased or vanished in the long term after 12 months [14, 15].

These results in the abovementioned studies illustrate the potential of implementing digital additions to conventional PR. A recent British study investigated a smartphone-based intervention for PR. That study aimed to compare the clinical delivery of a 6-week online PR program (myPR) to the current clinical standard face-to-face PR delivered in a conventional community setting in patients with COPD. The authors found that the app was noninferior to the outpatient program and did not influence the occurrence of adverse events [16]. The KAIA COPD app is available as a digital solution for pulmonary rehabilitation in German-speaking countries. The COPD app is comprised of an exercise training program and an educational program that was developed by health care professionals and PR experts. In a feasibility study, promising effects from a 20-day Intervention with, this digitalized PR program on CAT and HRQoL in severely symptomatic COPD patients were found [17]. However, until now, there has been no evidence for the efficacy of the COPD app from prospective studies, especially following PR.

We will conduct this randomized controlled trial (RCT) to determine the effects of the KAIA COPD app versus usual care on PA in patients with COPD following an inpatient PR program.

Our aim is to test a smartphone application for COPD patients that presents an educational and exercise training program plus activity monitoring and a motivational program that can be easily implemented in the patient’s home setting and that may enable patients to maintain the effects that are typically elicited in the short term after pulmonary rehabilitation for the long term. The overall objective of this project is to assess the effectiveness of this smartphone application for COPD patients in the maintenance of physical activity following PR. Activity monitoring will be provided by an activity tracker (Polar A 370, Polar Elektro GmbH, Germany).

### Objectives {7}

The overall objective is to assess the effectiveness of the newly developed COPD app as a maintenance program after PR. The primary objective is to assess the clinical efficacy of the COPD app maintenance program on physical activity measured in steps/day in patients with COPD after 6 months. The secondary objectives are to evaluate the effects of the COPD app program on functional exercise capacity, health-related quality of life (HRQoL), patient-reported health status, exacerbations, and depression and anxiety symptoms. Furthermore, we aim to explore patient compliance/adherence and safety, identify factors that facilitate the implementation of the program in the patient’s home setting, and evaluate factors of the program that are especially supportive for the patients.

### Trial design {8}

This trial is an international, multicenter, parallel-group, randomized, controlled study. Study participants are stage II–IV COPD patients who will be randomly assigned to the intervention group that will be provided with the KAIA COPD app or to a control group that will receive usual care. In total, 104 participants will be randomized (52 participants will be allocated to the intervention group and 52 to the control group). Two centers specializing in inpatient PR for COPD (Schoen Klinik Berchtesgadener Land, Germany and Zuercher RehaZentren Klinik Wald, Schweiz) will recruit study participants.

The estimated duration of the main study phase is planned to last approximately 1.5 years. All potential participants are COPD patients who are taking part in a regular inpatient PR program. The study started with screening of the first participant in August 2019. Enrollment of participants in the study is planned for a 12-month period. The last patient to complete the program is expected to finish in February 2021.

## Methods: participants, interventions, and outcomes

### Study setting {9}

The study will take place at hospitals specializing in rehabilitation programs for COPD patients of all stages (I–IV gold stages). At present, 2 study sites are participating in the trial: Pneumologie, Zürcher RehaZentren Klinik Wald, [name], Switzerland, and the Institute for Pulmonary Rehabilitation Research, Schoen Klinik Berchtesgadener Land, Schoenau am Koenigssee, Germany.

### Eligibility criteria {10}

During the recruitment period, all patients with COPD admitted to the PR hospitals will be informed about the ongoing study. Patients who are interested in study participation will receive oral and written information about the study before signing the informed consent for. After signing the informed consent form, participants will be instructed on how to use the activity tracker (Polar A 370) by the local study personnel. Participants will be instructed to wear the activity tracker every day for at least 20 h per day. After the screening period (approximately 8–10 days), eligibility will be judged by the local investigators based on the randomization criteria. If the screening requirements are fulfilled and the participants are deemed eligible, they will be randomized.

Every 2 weeks, an e-link leading to the questionnaires will be sent via email regarding exacerbations (questionnaire defined by the GOLD Guidelines), safety (adverse events or severe adverse events), device deficiencies, and patient feelings. There will be no prohibited medications during the study, and any change in concomitant medications will be noted down biweekly. In addition, at baseline and after 3 and 6 months, another e-link will be sent via email to all participants to complete the CRQ and HADS, to provide instructions to perform the 1-min sit-to-stand test and COPD Assessment Test (CAT), and to evaluate whether participants met their personal goal of physical activity.

Daily steps, sleep efficacy, and total sleep time will be passively collected by a Polar A 370 watch and will be imported to the study-specific electronic case report form (eCRF) system over the Google Fit Server. Figure 1 provides an overview of the study procedures.

**Fig. 1 Fig1:**
[figure not shown]
Provides an overview of the study conduct

The participants in the KAIA COPD app will be supplemented with a smartphone and access to the application together with the activity monitor. The participants in the control group will be supplemented with a smartphone and activity monitor. The smartphone is required in both groups to synchronize the daily steps from the activity monitor to the Polar website/database. These materials will be provided by KAIA Health Software GmbH for study purposes. At the end of the treatment period, the supplementary equipment will be collected from the participant.

#### Patient inclusion criteria

COPD patients willing and able to sign the informed consent form for use of their pseudonymized clinical data within the scope of the present interventional trialCOPD patients who have completed an in-hospital pulmonary rehabilitation program for an average duration of 3 weeksDiagnosis of COPD, defined as forced expiratory volume in 1 s/forced vital capacity (FEV1/FVC) < 70% predicted, FEV1< 80% predicted after bronchodilation, with or without chronic symptoms (cough, sputum production) corresponding to GOLD stage II–IVCompletion of an inpatient pulmonary rehabilitation programCompletion of the screening period and fulfillment of the randomization criteria as defined by the protocolAbility to use a smartphone and smartphone appsWillingness to wear an activity tracker during the 6-month study periodAge ≥ 40 years of ageKnowledge of German language to understand the study material, assessments, and contents of the COPD app

#### Patient exclusion criteria

The patient is unable to conduct the exercise training program due to physical, cognitive, or safety reasons, as judged by the investigators, e.g., lower limb joint surgery within the preceding 3 months, unstable cardiac diseases, predominant neurological limitations, and planned surgical or other interventions disturbing the study interventionSignificant psychiatric disorders, legal incapacity, or limited legal capacity. Patient participation in another clinical trial with an investigational medication within 30 days prior to study entryPatients already using the KAIA COPD app

#### Eligibility criteria during the screening period and before randomization

Completion of the training program for home settings, supervised by the study nurseDaily almost full-time wearing of the Polar watch (at least 20 h a day)

#### Procedures after randomization

The study nurse will carry out a short training program (20 min) to demonstrate the use of the wearable and mobile device platform and smartphone for both groups.

### Who will take informed consent? {26a}

Patients will be provided with a written informed consent form by the PI or the study staff delegated to obtain informed consent, such as a subinvestigator. Eligible patients will receive written information about all relevant aspects of the study and that their participation in the study is voluntary and they have the right to refuse or withdraw their consent at any time without reprisals. The study has been registered with the German Clinical Trials Register (DRKS00017275).

This paper contains the original study protocol. Any substantial modifications to the study protocol will be submitted to the corresponding country Ethics Committee for approval prior to implementation. These amendments will be documented in detail in the German Clinical Trials Register and will be described transparently in trial reports.

### Additional consent provisions for collection and use of participant data and biological specimens {26b}

On the consent form, participants will be asked if they agree to the use of their data should they choose to withdraw from the trial. Participants will also be asked for permission for the research team to share relevant data with people from the universities taking part in the research or from regulatory authorities, where relevant. This trial does not involve collecting biological specimens for storage.

### Interventions

#### Explanation for the choice of comparators {6b}

The control group will also wear the activity tracker every day and use the smartphone for the assessments but have no access to the content of the COPD app. The control group will also be an active control as participants will receive a leaflet to encourage an active lifestyle (“Besser leben mit COPD”) and an individually composed list of exercises for home training from experienced physiotherapists at the end of PR. This procedure represents the recent standard of care in this field. After finishing the study, at the 6-month assessments (visit 8), participants who were allocated to the control group will be offered the KAIA COPD app for free.

#### Intervention description {11a}

The study intervention consists of training sessions conducted daily by the patient via the COPD app. Regular contacts via telephone calls will be conducted by the same health care professional with respect to the realization and execution of the exercise training program shown in the COPD app. Patients will be contacted by phone if they do not meet the exercise criteria (exercising with the app at least 4 out of 7 days a week).

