### Participant timeline {13}

The study will take approximately 1.5 years to completion. The screening period is scheduled after a minimum of 7 days and a maximum of 14 days during inpatient rehabilitation. Once the participant enters the study and is randomized, the treatment period lasts for 6 months with biweekly follow-up for SAEs/AEs and device deficiencies. Any participant who is not responding to the visit emails will be followed up with 3 times until being considered lost to follow up. Figure 2 displays the study schedule in detail.

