#### Per-protocol analysis

As a sensitivity analysis, we will additionally conduct a per-protocol analysis, where we will also compare the control group with the intervention group but where we will only retain those participants in the intervention group who adhered to the intervention for the analyses.

We define adherence to the protocol (in terms of exercise training) as conducting the exercise training sessions for at least 70% of the weeks the patients are able to train (i.e., weeks when patients suffered from exacerbations or other health conditions that prevent them from training will not be considered; as discussed with the coach), for at least 4 times a week, during the 6 months of the intervention (see the following definitions):
Definition of a fulfilled individualized training session per day (according to the protocol: 3 different exercises per day are scheduled): completion of at least 2 different exercises per dayDefinition of a fulfilled week of training (rate of training sessions according to the protocol: 4 per week): completion of at least 4 out of the planned 7 individualized training sessions per week on average.

We will adjust the per-protocol analyses with prognostic factors for the primary outcome steps per day, lung function (FEV1), exercise capacity and exacerbation events, for adherence to conduction of the exercises (self-efficacy to conduct the exercises, exercise capacity, dyspnea, and acute worsening of health state [exacerbations and other]) and for whether the patients conducted other exercise strength training.

Concerning the control group, we will collect as much information as possible, especially with respect to the type and frequency of self-organized exercise training. This will also be included in the per-protocol analysis.

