#### Safety analysis

All adverse and serious adverse events that are recorded during the study will be described with regards to their severity grade, relationship to the COPD app intervention, and duration. The occurrence of adverse events and AEs overall between groups will be assessed with a two-tailed *t* test after the end of the follow-up.

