### Adverse event reporting and harms {22}

Adverse events (AEs) are defined as any untoward medical occurrence in a patient or clinical investigation participant after the intervention which does not necessarily have a causal relationship with the treatment. An AE can therefore be any unfavorable and unintended sign (including an abnormal laboratory finding), symptom, or disease temporally associated with the intervention, whether or not related to the intervention. An AE may also consist of a new disease, an exacerbation of a pre-existing illness or condition, a recurrence of an intermittent illness or condition, a set of related signs or symptoms, or a single sign or symptom.

Serious adverse event

A serious adverse event is defined as any event that
Requires inpatient treatment not envisaged in the protocol or extends a current hospital stay;Results in permanent or significant incapacity or disability;Is life-threatening or results in death; orCauses a congenital anomaly or birth defect.

All serious adverse events that occur after visit 1 will be collected in the eCRF. Medical conditions/diseases present before starting the study are only considered adverse events if they worsen after starting the study. Directly after registration, AEs and SAEs are judged by the PI to be related/not related or probably related to the intervention.

Adverse events occurring during the study will be recorded on the Adverse Events eCRF with the following information:
The severity grade (mild, moderate, severe)The relationship to the KAIA COPD app intervention (suspected/not suspected)The duration (start and end dates)

Once an adverse event is detected, it will be followed until its resolution or until it is judged to be permanent, and an assessment will be made at each contact (or more frequently, if necessary) of any changes in severity, the suspected relationship to the intervention, the interventions required to treat it, and the outcome.

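### The adverse-event comparison can count events first heard on training calls that only the app arm receives

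*Protocol article*

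**What the plan says.** **Common to both arms.** Eligibility criteria {10} sets the main route for finding events: "Every 2 weeks, an e-link leading to the questionnaires will be sent via email regarding exacerbations", and the same mailing covers safety. Participant timeline {13} applies to every randomized participant: "the treatment period lasts for 6 months with biweekly follow-up for SAEs/AEs and device deficiencies". It also provides three follow-up attempts for anyone who does not answer, before that person counts as lost. Outcomes {12} and Plans for assessment and collection of outcomes {18a} have participants complete assessments themselves, by link.

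**App arm only.** Intervention description {11a} states: "Regular contacts via telephone calls will be conducted by the same health care professional". The declared topic of these calls is how the app's exercises are being carried out. The section adds: "Patients will be contacted by phone if they do not meet the exercise criteria". The comparator text {6b} and the control-group steps under Implementation {16c} describe no such calls. The per-protocol definition of adherence excuses some weeks: "weeks when patients suffered from exacerbations or other health conditions that prevent them from training will not be considered; as discussed with the coach".

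**Recording and analysis.** Adverse event reporting and harms {22} has AEs entered on an AE eCRF with severity, relationship to the app and duration. It does not say that an AE must come from the e-link. It also counts the worsening of an existing illness as an AE. The Safety analysis section describes all recorded events and adds: "The occurrence of adverse events and AEs overall between groups will be assessed", by a two-tailed t test. The Abstract names exacerbation rate as a secondary outcome.

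**The concern.** A between-arm count of events is fair only if an event of the same kind has the same chance of reaching the record in each arm. Here the scheduled route is equal, but one arm has an extra channel. That channel is also linked to illness: a call is triggered when training drops, and the article itself gives exacerbations and other ill health as reasons why training drops. An app patient who leaves an event off the e-link may mention it when called about missed sessions. A control in the same state has no training call in which to mention it.

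The AE comparison carries the safety conclusion. If call-learned events enter the AE record, the error runs against the app and could suggest harm that is not there. COPD exacerbations fall under the article's AE definition, so they can enter the AE comparison this way. If they were also added to the exacerbation count, a true reduction could be masked.

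**Working it through.** The article gives no event rate, e-link completeness or detection rate for AEs or exacerbations, so there is no stated figure to reproduce. The check has two parts.

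**1. Can the text produce unequal counting?**

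- Scheduled detection: equal in both arms (Eligibility criteria {10}; Participant timeline {13}).
- Additional contact: regular and triggered training calls, app arm only (Intervention description {11a}). Explanatory outcomes mentions a phone call about personal goals without naming an arm, so controls may not be wholly without calls. It describes nothing like the regular training calls.
- Does the extra contact touch on illness? Yes, to the extent that weeks lost to illness are discussed with the coach (Per-protocol analysis).
- Is such an event barred from the AE record? No restriction by source is stated (Adverse event reporting {22}).
- Does the analysis separate sources? No. It takes all recorded events (Safety analysis), and the AE fields listed in the article do not include how the event was first learned.

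Each link is allowed by the text. None of the sections says that calls will in fact generate AE records.

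**2. How large could the effect be?** (illustration; all rates assumed)

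Let q be the share of true events captured by the e-link, equal in both arms. Let c be the share of the missed events that are picked up on calls and recorded, app arm only. With equal true rates:

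apparent ratio = (q + (1 − q)·c) / q

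For the chance of a false signal, assume a true mean of 1 event per patient, Poisson counts, 52 per arm, a two-sided 5% level and a normal approximation. With m1 = q + (1 − q)·c and m0 = q:

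d = (m1 − m0) / √((m1 + m0)/52)

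false-positive rate = Φ(d − 1.96) + Φ(−d − 1.96)

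| q | c | Ratio | False-positive rate |
|---|---|---|---|
| any | 0 | 1.00 | 5.0% |
| 1.00 | any | 1.00 | 5.0% |
| 0.90 | 0.25 | 0.925/0.90 = 1.03 | 5.2% |
| 0.90 | 0.50 | 0.95/0.90 = 1.06 | 5.8% |
| 0.80 | 0.25 | 0.85/0.80 = 1.06 | 5.9% |
| 0.80 | 0.50 | 0.90/0.80 = 1.13 | 8.6% |
| 0.60 | 0.25 | 0.70/0.60 = 1.17 | 9.7% |
| 0.60 | 0.50 | 0.80/0.60 = 1.33 | 23% |

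Worked case, q = 0.60 and c = 0.50: d = 0.20/√(1.40/52) = 0.20/0.164 = 1.22, so the rate is Φ(−0.74) + Φ(−3.18) ≈ 0.23.

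The first two rows are as compatible with the article as the rest.

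**The case against.** A reader might infer that events are found more often in the app arm and that the comparison is biased. The documents do not support that, for these reasons:

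- **The phrase about each contact concerns follow-up.** The words "an assessment will be made at each contact (or more frequently, if necessary) of any changes in severity" belong to a sentence about AEs that have already been detected. They do not make a training call a case-finding visit.
- **No passage has the coach asking about health systematically.** The stated subject of the calls is carrying out the exercises. Illness comes up only when weeks are excused from the adherence calculation.
- **Non-response is chased in both arms**, three times, so some missed e-links are recovered without any call.
- **Exacerbation rate is collected by the common e-link.** Classing an exacerbation as an AE does not make the AE record the source of that outcome.
- **The capture rates come from no document**, and 1.00 is within the range.
- **The article is condensed.** Source fields and counting rules may stand in the full protocol, the data management plan or the SAP.

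The first five points stand, and they reduce this to a conditional risk centred on AEs. They do not remove it. An equal schedule protects the comparison only if the e-link is complete or call-learned events stay out of the analysed record, and the article secures neither. Sample size {14} allows for 50% drop-out. That is not a measure of missed e-links, but it gives no ground for assuming complete reporting. On the last point, the article does set the comparison itself (all recorded AEs, regardless of source). If the full eCRF already captures the source, only the analysis rule remains to be stated.

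The remedy can also be challenged. A patient who has told the coach may not repeat the event on the e-link. If a share s of otherwise reported app-arm events were lost in this way, the e-link ratio with no true difference would be 1 − s, an error in the app's favour. This objection stands, and it is why an e-link comparison must not be the only one shown.

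**Conclusion.** The concern holds as a possible detection bias, mainly in the between-arm AE comparison. Followed as written, the plan can count app-arm events, first learned on intervention calls, that would go unrecorded in controls. With equal true rates the apparent ratio runs from 1.00 to about 1.33, across assumed e-link capture of 60% to 100% and call pick-up of 0 to 50%. The false-positive rate runs from 5% to 23% if the true mean is 1 event per patient. The documents supply none of these inputs, so the size cannot be narrowed, and no bias at all remains possible.

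The exacerbation rate is affected only if call-learned events are added to the e-link data, which the article does not say will happen. The primary outcome, steps from the tracker, is not affected.

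**What to change.** 1. Add a *source of first report* field to the AE eCRF (e-link, intervention call, other), unless the full eCRF already has one. If the source is not captured when the event is recorded, it cannot be separated reliably later.
2. State in the Safety analysis section that the between-arm test of AEs uses events reported through the e-link common to both arms.
3. State that exacerbation rate uses e-link reports only.
4. Continue to record and follow every AE and SAE however it was learned. Tabulate all of them by arm and source, and show the all-events comparison beside the e-link comparison.

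The cost is one eCRF field, two or three sentences and one extra table. The downside is that an app-arm event told to the coach and not repeated on the e-link is missing from the like-for-like test. The all-events table is kept for that reason, and any difference between the two comparisons should be discussed when the safety results are reported.
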